## Abstract

**Background:**

Preliminary evidence suggests that palliative care may be useful for people with severe multiple sclerosis (MS). The aim of this study is to determine the effectiveness of a home-based palliative approach (HPA) for people with severe MS and their carers.

**Methods/design:**

This is a single-blind randomized controlled trial with a nested qualitative study. Seventy-five severe MS-carer dyads are being randomized (at three centers, one in each area of Italy) to HPA or usual care (UC) in a 2:1 ratio. Each center has a specially trained team consisting of four professionals (physician, nurse, psychologist, social worker). The team makes a comprehensive assessment of the needs of the dyads. HPA content is then agreed on, discussed with the patient’s caring physician, and delivered over six months. The intervention is not intended to replace existing services. At later visits, the team checks the HPA delivery and reviews/modifies it as necessary.

HPA and UC dyads are assessed at home by a blind examiner at baseline, and three and six months later; they also receive monthly telephone interviews. Dyads assigned to UC receive the examiner’s visits and telephone interviews, but not the team visits.

Primary outcome measures are changes in symptoms (Palliative care Outcome Scale-Symptoms-MS, POS-S-MS), and quality of life (the Schedule for the Evaluation of Individual Quality of Life-Direct Weighting (SEIQoL-DW), not assessed in patients with severe cognitive compromise) at three and six months. Other outcomes are changes in patient functional status and mood; changes in carer quality of life, mood and caregiving burden; costs; incorporation with standard care; unplanned hospital admissions; referrals to hospice; and deaths.

The experience of participants will be evaluated qualitatively by individual semi-structured interviews (HPA patients and carers) and focus group meetings (HPA patients’ caring physicians).

**Discussion:**

The results of our study will show whether the HPA is feasible and beneficial to people with severe MS and their carers living in the three Italian geographic areas. The nested qualitative study will add to the understanding of the strengths and limitations of the intervention.

**Trial registration:**

The trial was registered with Current Controlled Trials (identifier: ISRCTN73082124) on 19 June 2014.

## Background

Multiple sclerosis (MS) is the most common disabling neurological condition of young adults in western countries. It affects over 2.5 million people worldwide, and evidence suggests that incidence is increasing [1]. Around 15% of MS sufferers have a progressive course from the outset (primary progressive MS), and a further 65% develop progressive disease after a variable period with relapsing-remitting disease (secondary progressive MS) [2]. For those with primarily or secondarily progressive MS, treatment options to delay or prevent further clinical worsening are limited. Reduced mobility and compromised sphincter control are among the commonest symptoms, but cognitive impairment, swallowing or speech impairment, pain and sensory disturbances may also be prominent [3-5]. Patients with severe MS are at risk of death from aspiration pneumonia, urinary tract infections, complications of falls and fractures, and sepsis secondary to pressure ulcers. Nevertheless, some highly disabled patients live for many years, although most die in hospital rather than at home [6].

Although robust evidence supporting treatment decisions in advanced MS is lacking, recent guidelines suggest shifting to a palliative approach as the disease worsens [7]. Palliative care, with its focus on the physical, psychological, spiritual and social needs of patients and families, and their active involvement in medical decisions, aims to improve the quality of care and reduce the use of emergency and acute care services. However, palliative care has traditionally been delivered in oncology, and is little used in MS and other neurological diseases. There are issues that are specific to MS: for example, pain due to spasticity requires a different approach to cancer pain management, and cognitive and communication compromise may hamper ability to reveal experiences and express choices. Furthermore, it is difficult to anticipate life expectancy in people with severe MS, who may sometimes need palliative care over an extended period.

It is noteworthy that recent studies on adults with severe MS and their carers [8-11], and also newly diagnosed persons with MS [12,13], indicated similar areas of concern comprising insufficient time spent with health professionals, lack of information exchange, and discontinuity of care.

The current trend of managing chronic and terminal conditions in the community entails the need to implement effective home care models. Informal carers are an essential source of support for MS patients, and in advanced disease informal carers take responsibility for meeting most of their patient’s needs, thereby preventing patient institutionalization. However, the caregiving burden can lead to a decline in carers’ health-related quality of life (HRQOL) and adversely affect their employment and finances.

Evidence supporting a benefit of palliative care is sparse, with most studies assessing needs instead of interventions, or having methodological flaws [14]. We found two randomized controlled trials (RCTs) on the efficacy of palliative care in people with severe MS [8,15]. The UK trial showed that a home-based palliative care service improved symptoms management, reduced caregiver burden and the use of primary and acute hospital services over the short term [8]. The Italian trial (Ne-Pal) included people with severe MS, Parkinson’s disease and related disorders, and amyotrophic lateral sclerosis; the home-based palliative care intervention improved patient HRQOL and some symptoms [15]. Nevertheless, it may not be straightforward to transfer interventions of this sort to different contexts and health systems [16,17].

### Objectives

The primary aim of the present study is to determine the effectiveness of a home-based palliative approach (HPA) on MS symptoms and HRQOL of people with severe MS. Secondary outcomes are changes in patient functional status and mood; changes in carer HRQOL, mood and caregiving burden; costs; incorporation with standard care; unplanned hospital admissions; referrals to hospice; and deaths over the six-month intervention.

## Methods

### Ethical approval and trial registration

The study was given ethical approval by the Foundation IRCCS Neurological Institute ‘C. Besta’ (Besta internal reference numbers 6, 11), the Foundation ‘S. Lucia’ Hospital (internal reference number CE/OSS.27), and the University Hospital of Catania (internal reference number 18/2014/PO) Ethics Committees. The trial is registered with Controlled Clinical Trials (trial registration number ISRCTN73082124).

### Trial design

This is a multicenter phase II/III single-blind randomized controlled trial. Participants (dyads of adults with severe MS and their carers) are randomized to either the HPA intervention group or usual care (UC). Figure 1 presents the PeNSAMI trial flowchart.

**Figure 1 Fig1:**
[figure not shown]
The PeNSAMI trial flowchart. ^*^Visits 1 to 3 performed by a blind examiner;  phone interviews performed by a trained interviewer. HPA, home-based palliative approach; UC, usual care.

#### Inclusion and exclusion criteria

All adults (18 years or older) who fulfill all the following criteria are potentially eligible:Diagnosis of MS [18]Expanded Disability Status Scale (EDSS) ≥8.0 [19]Primary or secondary progressive coursePresence of a carer (family member, relative, or friend, who is next of kin or is key decision maker as designated by the (cognitively competent) MS patient and with whom the patient shares his/her life)At least two unmet care needs among the categories identified in the PeNSAMI Phase 1 qualitative study (Table 1) [11], or the patient declares for comfort care only

**Table 1 Tab1:** **List of main care need categories, as identified in the PeNSAMI Phase 1 qualitative study** [11]

**Domain**	**Category**
**‘** ***Managing everyday life*** **’**	Symptoms management
	Personal care/hygiene
	Activities of daily living
	Outdoor mobility and transport
**‘** ***Psychosocial*** **’**	Relationships/communication
	Leisure/holidays
	Psychological well-being/social role
**‘** ***Organization*** **’**	Information
	Access to services
	Co-ordination of services
	Competent professionalsOne or more of the following: significant complex symptoms/medical complications, dysphagia/poor nutritional status, communication difficulties [20].

Exclusion criteria are:Hospitalized/institutionalized patientsPatients already receiving palliative careDyads living out of study area

#### Recruitment

Starting on 10 January 2015 participants are being recruited from the three participating centers. Recruitment closes at the end of June 2015.

#### Informed consent and pre-study evaluation (Visit 0)

Potentially eligible patients are identified by the center principal investigator (PI) by consulting the MS center database and by contacts with general practitioners (GPs), and other health personnel involved in the care of severely affected MS patients. MS patient and their carer are approached by a HPA team member to give informed consent to participate. If consent is obtained, baseline electronic case record forms (eCRFs) are completed.

#### Baseline visit (Visit 1)

After pre-study evaluation, participants identified as meeting the eligibility criteria are assessed at home by the blind examiner who confirms the inclusion criteria, administers the outcome instruments and initiates the randomization procedure. A card showing the time and date of the three- and six-month follow-up visits is given to the dyad.

#### Randomization

Eligible study participants are randomized to either HPA or UC using third-party, web-based computerized randomization software. A stratified minimization algorithm is used to ensure balance of possible prognostic factors across the two groups (EDSS (8.0 to 8.5, 9.0 to 9.5), presence of severe cognitive compromise (clinical judgment), and center (Milan, Rome, Catania)). Following randomization, an email informing on dyad assignment is sent to the PI and the HPA team. The team informs the dyad about assignment. The team also contacts the patient’s caring physician (GP, neurologist or other physician responsible for the patient’s care) to inform him/her about the study and (for dyads assigned to HPA) define a common agenda.

#### Blinding

To reduce measurement bias, the baseline and follow-up assessments are performed by independent examiners blind to treatment assignment (one examiner plus backup at each center, both trained, neither involved in HPA delivery). Prior to each follow-up visit, study dyads will be reminded not to disclose their allocation by mentioning any contact with the HPA team to the blind examiner. The examiner will be asked to guess dyad status (HPA vs. UC) after the three- and six-month visits to assess whether blinding is maintained.

#### HPA group

The trial intervention is based on the principles of palliative care as described in the 2010 guidance document of the UK National Council for Palliative Care, Neurological Alliance, and National End of Life Care Programme [21]. Each center has a HPA team consisting of four professionals: a physician (neurologist, physiatrist or palliative specialist), nurse, psychologist, and social worker. The HPA team nurse is the case manager and team leader: the nurses of the centers of Milan and Rome have degrees in palliative care; the Catania nurse attended a FARO Foundation week-long individual training course in September 2014. All HPA team members were trained in the HPA intervention at the FARO Foundation, Turin, 20 to 21 February 2014. HPA teams will meet about two months after trial initiation (more often if necessary) to share experiences and fine-tune the protocol.

Each HPA team meets regularly to discuss the management of dyads in their charge. Initially, the team forms a comprehensive assessment of each dyad based on information provided by the blind examiner visit (available to the HPA team via the eCRF and the web-based information system) and that provided by the team home visit. The HPA content for each dyad is then developed, discussed with the caring physician, and delivered over six months, with involvement of local services. The intervention is not intended to replace existing services but to complement and enhance them, minimizing duplication of effort. Subsequently, the HPA team verifies program implementation, and reviews and modifies it as necessary.

Home visits by one or more team members will take place at least twice a month in the first trimester, and as needed thereafter. Which professionals attend for home visits depends on the intensity of care and the type of symptoms (for example physician for pain management, nurse for bed sore treatment). A dedicated phone number is given to dyads to enable easy communication with the HPA team. The team is not on call for patients: in the event of emergencies, dyads contact the caring physician or emergency medical services.

We expect HRQOL and other study outcomes to improve in the first trimester, so thereafter frequent home visits could be useless or intrusive [15]. However, if symptoms and HRQOL worsen, or end of life issues manifest, intensity of care will be maintained or increased. All HPA team activities/interventions will be recorded in the patient study record, kept at the patient’s home and available to all health professionals/caregivers. To preserve blinding, before visits 2 and 3, dyads will be reminded to keep the patient study record out of the blind examiner’s sight (for example by placing it in a drawer).

#### UC group

UC consists of the health and social services normally provided by the Italian National Health Service in the study area (for example by GP, district nursing service, social services, neurologists and other specialists, and emergency services). Patient-carer dyads assigned to UC receive the three blind examiner visits and the monthly telephone interviews, but not the HPA team visits (except Visit 0). At the end of the study, dyads who received UC will be offered the HPA.

#### Primary outcomes

Primary outcomes are changes in patient HRQOL (Schedule for the Evaluation of Individual Quality of Life-Direct Weighting, SEIQoL-DW) and MS symptoms (Palliative care Outcome Scale-Symptoms-MS, POS-S-MS). The SEIQoL-DW is a brief instrument, derived from the schedule for evaluation of individual quality of life (SEIQoL). It allows respondents to nominate areas of life that are most important in determining their HRQOL. The level of satisfaction/functioning in each of these areas is then recorded [22-26]. The SEIQoL-DW index is obtained from the satisfaction with and weighting for each area, and ranges from 0 (worst possible score) to 100 (best possible score). SEIQoL-DW has been used in neurological diseases [27-30], and was the primary outcome measure of the Ne-Pal trial [15].

POS-S-MS (primary outcome measure) and the Core-Palliative care Outcome Scale (Core-POS) were developed and validated for use with palliative care patients to assess emotional, psychological and spiritual needs, and provision of information and support [31,32]. Core-POS has been used in patients with advanced cancer and other conditions including dementia, motor neuron disease, and MS [33,34]. It consists of 10 items, which are scored from 0 (best) to 4 (worst). The score is the sum of the scores from each question, and therefore can range from 0 to 40. There are patient, carer, and staff versions, each requiring about 10 minutes to complete [31,35]. Generally, the patient is asked about needs over the preceding three days, but other time frames have been used [36]: in this study, we asked about the preceding seven days.

POS-symptoms (POS-S) is a scale enquiring about 10 symptoms with two open questions (which symptom affected the patient the most; which improved most). It was developed for use in cancer patients and is used alongside the Core-POS for assessing common physical symptoms. Disease-specific versions of POS-S have been developed for end-stage kidney disease, Parkinson’s disease, and MS [33]. POS-S-MS comprises 18 items relating to MS symptoms, plus an open question (0 to 4 scale) over the preceding seven days [34].

The psychometric properties of Core-POS and POS-S-MS have been assessed in patients with severe MS: both are acceptable, reliable, and valid in this population [34].

In the present RCT, MS patients with severe cognitive impairment do not complete the questionnaires: the caregiver versions of Core-POS and POS-S-MS are used.

#### Secondary outcomes

Secondary outcome measures are HRQOL as assessed by Core-POS [34] and European Quality of Life Five Dimensions (EQ-5D) [37,38]; mood as assessed by the Hospital Anxiety and Depression Scale (HADS) [39,40]; impairment/activity limitations as assessed by EDSS [19] and Functional Independence Measure (FIM) [41,42]; and direct and indirect tangible costs are assessed by the MS foundation Costs Questionnaire (MSCQ) [43].

Carer outcomes are: HRQOL as measured by Short Form 36 (SF-36) [44,45] and EQ-5D; mood as measured by the HADS; and carer burden as measured by the Zarit Burden Interview (ZBI) [46,47].

Recruitment rates, reasons for exclusion, time to delivery of interventions, adherence to intervention (see the HPA group), protocol deviations, incorporation with standard care, unplanned hospital admissions, referrals to hospice, deaths (place and cause) are also considered over the six-month period.

Outcome assessments (Table 2) are carried out at baseline, and after three and six months, by a blind examiner at the patient’s home. In addition, six telephone interviews are performed, on a monthly basis, by a trained interviewer who administers the full MSCQ (at three and six months) and pertinent MSCQ sections (at one, two, four and five months).

**Table 2 Tab2:** **Outcome measures and timing of follow-up**

	**Baseline**	**Three-month follow-up**	**Six-month follow-up**
General characteristics	X	X	X
MS history	X	X	X
Medical history	X	X	X
EDSS	X	X	X
FIM	X	X	X
SEIQoL-DW^*^	X	X	X
Core-POS^**^	X	X	X
POS-S-MS^**^	X	X	X
HADS^*^	X	X	X
EQ-5D^*^	X	X	X
MSCQ	X	†	†
Carer characteristics /medical history	X	X	X
Carer HADS	X	X	X
Carer SF-36	X	X	X
Carer EQ-5D	X	X	X
Carer ZBI	X	X	X

To preserve blinding, all outcome measures (except MSCQ) are assessed during examiner visits at three and six months follow-up. ^*^Not assessed in MS patients with severe cognitive compromise or unable to communicate; ^**^carer versions used in MS patients with severe cognitive compromise or unable to communicate; ^†^assessed by phone interview. Core-POS, Core-Palliative care Outcome Scale; EDSS, Expanded Disability Status Scale; EQ-5D, European Quality of Life Five Dimensions; FIM, Functional Independence Measure; HADS, Hospital Anxiety and Depression Scale; MSCQ, Multiple Sclerosis foundation Costs Questionnaire; MS, multiple sclerosis; POS-S-MS, Palliative care Outcome Scale-Symptoms-Multiple Sclerosis; SF-36, Short Form 36; SEIQoL-DW, Schedule for the Evaluation of Individual Quality of Life-Direct Weighting; ZBI, Zarit Burden Interview.

#### Safety

We expect no serious psychological, physical, social, or legal risks to derive from exposure to the study intervention. We cannot exclude, however, that the study intervention will have a negative effect on patient status. The following serious adverse events (SAEs) are being monitored:Emergency room visits that do not result in hospital admissionHospitalizations (overnight stay at hospital or emergency room for observation or treatment)Death (any cause)

Hospitalization for elective surgery, routine or planned clinical procedures are not considered SAEs.

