#### Independent data and safety monitoring committee (IDSMC)

The IDSMC monitors SAE reports throughout the trial, and oversees trial progress, ensuring that it is conducted, recorded, and reported in accordance with the protocol, good clinical practice, and applicable regulatory requirements. The IDSMC provides recommendations about stopping or continuing the trial in the event of harm, undue risks, or futility. IDSMC members (Appendix 1) met (via teleconference) prior to the start of enrolment. Subsequent IDMSC teleconferences are scheduled every four months, and at trial termination, or more frequently as necessary.

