### Expected benefits

Fragmentation of care across different health care sectors is a recognized problem, particularly for patients with complex care needs and co-morbidities. The HPA is not intended to replace existing services but to complement, collaborate with, and enhance them, minimizing duplication of effort. The potential for HPA integration into existing services is a strength of our trial.

Health professionals caring for people with severe MS themselves have several unmet needs and feel overstretched in their daily work. Physicians express feelings of helplessness or anger in the face of cuts in funding, and having to work under time pressure and in complex social situations [11]. They also feel hampered by inadequate communication skills (not taught at university) [10,56].

In addition to providing valuable data, the trial affords interdisciplinary training for the health professionals involved. By making palliative care professionals work with MS neurology and rehabilitation professionals [57], the trial should encourage greater awareness and more effective management of people with severe MS.

Effective exchange between the dyad, the caring physician and the HPA team should result in treatment decisions in the best interests of MS patients and the avoidance of inappropriate hospital admissions. It is also expected that the trial will empower people with severe MS (and their carers) by providing them with information and education on their condition, encouraging them to be active participants in care and decision making, including advance health directives where appropriate.

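### Every non-fatal SAE is an emergency-room or hospital contact, which the palliative approach is expected to reduce, so a lower SAE count under HPA could mean less hospital use and not fewer serious events

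*Protocol article*

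**What the plan says.** All references are to the protocol article.

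- **Safety.** The section expects no serious risks but adds: "We cannot exclude, however, that the study intervention will have a negative effect on patient status". Three SAEs are then listed. The first is an emergency-room visit without admission. The second is hospitalization, defined as "overnight stay at hospital or emergency room for observation or treatment". The third is death from any cause. There is one exclusion: "Hospitalization for elective surgery, routine or planned clinical procedures are not considered SAEs".
- **Background.** Palliative care is said to aim, among other things, to "reduce the use of emergency and acute care services". The earlier UK trial is summarised as having reduced use of primary and acute hospital services. Patients with severe MS are described as "at risk of death from aspiration pneumonia, urinary tract infections, complications of falls and fractures, and sepsis secondary to pressure ulcers".
- **Expected benefits.** Good exchange between dyad, caring physician and HPA team should lead to "the avoidance of inappropriate hospital admissions".
- **Objectives and Secondary outcomes.** Unplanned hospital admissions are a secondary outcome over the six months.
- **HPA group.** Team members visit at home, with bed-sore treatment by the nurse given as an example. The team is not on call, and dyads take emergencies to the caring physician or emergency services.
- **IDSMC.** "The IDSMC monitors SAE reports throughout the trial". The committee also oversees trial progress and can recommend stopping for harm, undue risk or futility.

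**The concern.** The stated risk is a worsening of the patient's condition. The non-fatal SAE list does not measure that. It measures whether the patient came into contact with a hospital or emergency room. No criterion refers to how ill the patient was.

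This would matter little if the route from complication to hospital were the same in both arms. The article gives reason to expect that it may not be, because reduced acute-care use is part of what palliative care is meant to achieve. An aspiration pneumonia that leads to admission is an SAE. The same pneumonia treated at home is not. If the share treated at home differs by arm, ascertainment of serious events differs by arm too.

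At stake is how the SAE comparison is read, both by the committee during the trial and in the final report. A favourable SAE ratio would be hard to interpret, and an excess of non-fatal complications could be partly hidden.

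**Working it through.** The plan states no figure on this point, so there is none to reproduce. The check has two parts.

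**1. The passages side by side**

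- Non-fatal SAE criteria (Safety): two, both defined by service use. Criteria based on clinical severity: none.
- Once elective, routine and planned hospital stays are excluded, the hospitalization SAE is close to the same event as the secondary outcome of unplanned admissions. One event thus serves both as a measure of benefit and as a signal of harm.
- The complications named in Background (aspiration pneumonia, urinary infection, falls and fractures, sepsis from pressure ulcers) enter the SAE data only through hospital or emergency-room contact, or death.
- Expected direction of hospital use under palliative care (Background, Expected benefits): downward.

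**2. What this can do to the count (illustration only)**

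Inputs from the article: 50 HPA and 25 UC patients (Sample size). Everything else is assumed: the six-month risk of a serious non-fatal complication in each arm (pH, pU), and the share of complications that reach hospital or the emergency room (hH, hU).

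Counted ratio = (pH × hH) / (pU × hU) = true ratio × (hH / hU).

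Take hU = 0.80 throughout.

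| Assumed risk HPA vs UC | True ratio | hH = 0.80 | hH = 0.60 | hH = 0.40 |
|---|---|---|---|---|
| 30% vs 30% | 1.00 | 0.24/0.24 = 1.00 | 0.18/0.24 = 0.75 | 0.12/0.24 = 0.50 |
| 40% vs 30% | 1.33 | 0.32/0.24 = 1.33 | 0.24/0.24 = 1.00 | 0.16/0.24 = 0.67 |
| 30% vs 20% | 1.50 | 0.24/0.16 = 1.50 | 0.18/0.16 = 1.12 | 0.12/0.16 = 0.75 |

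In the first row, 50 × 0.30 = 15 HPA patients have a complication. Those not counted as SAEs number 15 × (1 − hH) = 3, 6 or 9. In the UC arm, 25 × 0.30 = 7.5 have one and 7.5 × 0.20 = 1.5 are not counted.

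Writing s = 1 − hH/hU for the fraction shifted from hospital to home, the counted ratio is true ratio × (1 − s):

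- No true difference, s = 20% to 40%: 1.00 × 0.80 to 1.00 × 0.60 = 0.80 to 0.60.
- True 25% excess, s = 30%: 1.25 × 0.70 = 0.875.
- Shift that exactly hides an excess: s = 1 − 1/(true ratio), which is 20% for 1.25, 25% for 1.33 and 33% for 1.50.

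**Precision.** Take an assumed counted UC risk of 30% and a counted ratio of 0.875, so 7.5 of 25 against 13.125 of 50. The standard error of the log ratio is √(1/13.125 − 1/50 + 1/7.5 − 1/25) = √0.1495 = 0.387. The 95% interval is 0.875 × exp(±1.96 × 0.387), about 0.41 to 1.87. A single comparison of this size would establish neither benefit nor harm. The distortion lies in where the estimate is centred.

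**The case against.** The other side has several good points, and most of them stand.

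- **Emergencies follow the same route in both arms.** The HPA team is not on call, and the article describes the approach as activating existing services, not as hospital care at home. This narrows the difference in ascertainment. It does not remove it, because fewer admissions remain an expected effect.
- **Only inappropriate admissions are targeted.** This is correct. But the SAE list does not separate them from appropriate ones, so any fall shows in the same count.
- **Patient status is measured elsewhere.** The blind examiner records POS-S-MS, Core-POS, EDSS, FIM and medical history at baseline, three and six months in both arms, with carer versions of the POS scales where needed. Deaths are recorded with place and cause. A reader might infer that the trial cannot judge safety at all. That is not supported: the limitation applies to the SAE data.
- **Under-treatment may still surface.** A reader might infer that under-treatment would register as a safety benefit. The documents do not support that either. HPA adds to usual services, and under-treatment could equally lead to emergency visits, admissions or deaths, all of which count.
- **The committee is not confined to SAE counts.** Its remit covers trial progress, harm and futility, and the contents of its reports belong in a charter that is not shown. No criticism of those contents is made here.
- **Hospital contacts and deaths are objective and verifiable.** This is a real advantage when dyads know their allocation. It is a reason to keep these categories, but not to have only these.

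**Conclusion.** The point holds in a limited form. The article itself fixes an SAE list in which every non-fatal event is an emergency-room visit or hospitalization, and it expects palliative care to reduce such use. Applied as written, the list can make SAE ascertainment depend on arm. A lower SAE count under HPA could then reflect less hospital use and not fewer serious events, and the SAE data alone cannot separate the two.

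The size cannot be determined from the documents. The shift of 20% to 40% and the true excess of 25% are illustrative assumptions, as are the risks in the table. They show that the direction of the counted ratio can change; they do not show that it will. The conclusion also assumes that some serious complications are managed at home more often under HPA than under UC, which the article makes plausible but does not state. The primary outcomes are unaffected.

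**What to change.** 1. Add one SAE category that does not depend on setting: life-threatening events and the serious complications already named in Background, wherever treated, each with a fixed written definition.
2. Record it identically in both arms through two existing contacts: a short fixed checklist in the monthly telephone interview, and the blind examiner's medical history at three and six months. Any question on where or by whom the event was treated should stay with the telephone interviewer, so that the examiner is not unmasked.
3. Keep deaths, hospitalizations and emergency-room visits as recorded, but also report hospital and emergency-room use separately as a service-use outcome, so that a fall in use is not presented as a fall in serious events.

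The cost is a few extra questions on calls and visits already scheduled, definitions to write, and a higher SAE count to process. No new visits or staff are needed. One drawback remains: the telephone answers come from dyads who know their allocation, and HPA dyads are visited at least twice a month in the first trimester, so complications may be recognised more readily in that arm. The blind examiner's record offsets this in part. The change concerns what is counted, not how any patient is treated.
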